### Randomization

Bahir Dar city is divided in to two parts by the Nile River. From these two parts of the city, one will be randomly selected as the control area using a coin tossing randomization procedure by a principal investigator, and the other will assign as the intervention site. To reduce information contamination, bank employees who work in the control area will make up the control group, whereas bank employees who work in the intervention area will make up the intervention group. The data collectors, the nurse who will offer general advice to the control group, the education provider for intervention group, and the participants will all be blinded to the group assignment. Finally, each individual participant will be screened based on the inclusion and exclusion criteria, up until the target sample size is reached.

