**Methods and analysis:**

This randomized controlled trial will be implemented with 226 bank employees (age ≥18 years) with metabolic syndrome from government and private banks in Bahir Dar City, Ethiopia. Participants will be randomized to intervention (education) and control (general health advice) groups. The intervention group will be given one-on -one base education about healthy diets, physical exercise, stress management, avoidance of harmful alcohol consumption and smoking cessation by experts on health promotion. Text messages will be sent every two weeks and reading materials will also be provided. Additionally, a review meeting will be held at the 3^rd^ and 6^th^ month of the intervention. The primary outcomes of interest will be change in metabolic parameters (obesity levels, blood pressure, fasting blood glucose, total cholesterol, high density lipoprotein, low density lipoprotein, and triglycerides). Secondary outcomes will be knowledge, attitudes and practice of the participants towards lifestyle and cardiovascular risk factors, feasibility, acceptability, implementation fidelity, and cost-effectiveness of the intervention. Data will be collected at three time points: at baseline, at the 6^th^ month of the intervention and at the end of the intervention (9 months). Generalized linear mixed models will be utilized to compare the desired outcome between the trial arms, after accounting for baseline variations. Cost-benefit analysis and a qualitative process evaluation of the intervention will also be conducted.

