## Methods

### Study design

A randomized control trial using a parallel design will be employed to develop and test the effectiveness, feasibility, and acceptability of lifestyle intervention on metabolic syndrome management, and to assess and compare the levels of knowledge, attitudes, and practices towards lifestyle and cardiovascular risk factors before and after the intervention as well as between the control and intervention groups among bank employees with metabolic syndrome, and also to evaluate the cost effectiveness and the implementation process of the intervention. The trial has been designed according to the Standard Protocol Items: Recommendations for Interventional Trials (SPIRIT) (**S1 File**). It is registered with the Australian New Zealand Clinical Trials Registry (ACTRN12623000409673p).

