### Study setting

The study will be conducted in the Bahir Dar city, Ethiopia, among bank workers. Bahir Dar is located 565 km Northwest of Addis Ababa and it is the capital city of the Amhara regional state. There are 210 bank branches with 2,310 workers in the city.

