### Statistical analysis

The analysis will follow modified intention-to-treat principles (based on group randomized to and using all available data but without being able to directly assess the impact of the intervention being offered to those for whom we do not have follow-up data and where their outcome data are not missing at random). Descriptive statistics means (standard deviations), medians (interquartile ranges), frequencies (relative frequencies) will be used to summarize participant’ characteristics and study outcomes. Epi Data (double entry) will be used to enter the quantitative data and it will be analyzed using Stata 13.1 or later versions, with p<0.05 considered significant. Generalized linear mixed models (GLMM) will be used to assess the impact of the intervention on the change of metabolic syndrome components, as well as on the knowledge, attitudes and practice of participants on healthy lifestyle. The metabolic syndrome indicators (Obesity level, BP, FG, HDL, and TGL), knowledge, attitudes, and practices towards lifestyle and cardiovascular risk factors will be the outcome variables, and age, sex, marital status, educational status, work experience, working hours per day, monthly income, religion, health condition, and level of KAP will be the independent variables of the study.

All items in the CONSORT statement will be followed when reporting, and a CONSORT flow diagram will be included to indicate participant flow and, if available, the causes of exclusion and loss to follow-up (**Fig 1)**. The effectiveness of the intervention will be assessed using differences in changes in the metabolic syndrome indicators (Obesity level, BP, FG, HDL, and TGL) between groups from baseline to nine months. As well as, by assessing knowledge, attitudes, and practices towards lifestyle and cardiovascular risk factors before and after the intervention as well as between the control and intervention groups.

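### One coin toss assigns the two halves of the city, so there is one randomised unit per arm, and no model can give an SE or p-value that includes area-specific change over the 9 months

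*Protocol article*

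**What the plan says.** The abstract (Methods and analysis) states: "Participants will be randomized to intervention (education) and control (general health advice) groups". The Study design section uses the same label, "A randomized control trial using a parallel design will be employed", and does not mention clusters.

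The Randomization section describes a different mechanism. It begins "Bahir Dar city is divided in to two parts by the Nile River" and continues that "one will be randomly selected as the control area using a coin tossing randomization procedure"; the other part becomes the intervention site. Arm then follows workplace: "bank employees who work in the control area will make up the control group, whereas bank employees who work in the intervention area" form the intervention group. The stated reason is to limit contamination. No later step randomises branches or individuals. The section ends: "Finally, each individual participant will be screened based on the inclusion and exclusion criteria, up until the target sample size is reached".

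The Sample size section uses the formula for two independent means, with 80% power and 94 per group, and applies no design effect. The Statistical analysis section plans generalized linear mixed models with person-level covariates, a p<0.05 criterion, and a comparison of changes from baseline to nine months. The abstract adds adjustment for baseline. The only limitation named in the Discussion is that the intervention is not tailored to each individual.

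**The concern.** Arm and area are the same variable in this design. If systolic pressure, glucose or waist circumference changes differently on the two sides of the river over nine months for reasons unrelated to the education, that difference enters the intervention estimate in full. Nothing inside the trial can reveal how large it is.

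The plan nevertheless presents a randomised comparison of employees with 80% power at 5% error. The Introduction expects the results to inform policy makers on scale-up. A significant result would be reported as individually randomised evidence, which this allocation does not produce.

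**Working it through.** **1. The plan's own figure.** Inputs from the Sample size section: SDs 15.0 and 16.3, means 107.8 and 114.2, z values 1.96 and 0.84.

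n = (15.0² + 16.3²)(1.96 + 0.84)² / 6.4² = 490.69 × 7.84 / 40.96 = 93.9, so 94 per group and 188 in total. The figure reproduces, as a calculation for independently allocated individuals.

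**2. Randomised units.** There are two areas and one coin toss, hence 2 units, 1 per arm.

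- Between-area degrees of freedom = areas − arms = 2 − 2 = 0.
- Only 2 allocations were possible. A randomisation test therefore cannot give a p-value below 1/2 one-sided or 2/2 = 1 two-sided.
- In a model of change, the arm-by-time term and an area-by-time term are the same column. An area fixed effect or random intercept cannot separate them. A branch random intercept would handle correlation within branches but not the area term.

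None of step 2 depends on an assumed ICC.

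**3. Illustrative size.** The documents give no area-level ICC; I assume 0.001 to 0.05. The outcome is unadjusted systolic pressure with SD = √(490.69/2) = 15.66 mmHg and m = 94 analysed per arm.

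- Design effect: DE = 1 + (94 − 1) × ICC.
- True error of a nominal 5% test that ignores area: 2 × [1 − Φ(1.96/√DE)].
- Power for 6.4 mmHg if the area variance were known: Φ(6.4/SE − 1.96), with SE = 15.66 × √(2 × DE/94).
- Floor of the SE however many employees are added: 15.66 × √(2 × ICC).

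| Assumed ICC | DE | True error | Power | SE floor (mmHg) |
|---|---|---|---|---|
| 0 | 1.00 | 5% | 80% | 0 |
| 0.001 | 1.09 | 6% | 76% | 0.7 |
| 0.01 | 1.93 | 16% | 52% | 2.2 |
| 0.05 | 5.65 | 41% | 22% | 5.0 |

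The stated 80% power and 5% error correspond to the first row only. The power column is generous, because two areas cannot supply the area variance that it takes as known.

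**4. Effect of baseline adjustment.** Assume, again for illustration, a baseline-to-follow-up correlation of 0.9 at area level and 0.5 at individual level. An ICC of 0.01 then becomes (0.19 × 0.01) / (0.19 × 0.01 + 0.75 × 0.99) = about 0.0026. DE is about 1.24 and the true error about 8% instead of 16%. If the two correlations are equal, nothing is gained.

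**The case against.** The plan is not without safeguards. It compares changes from baseline, adjusts for baseline, and lists income and other personal characteristics as covariates. A reader might infer that every difference between the two sides of the river is confounded with treatment; that goes too far, because stable, measured differences are at least partly handled. What remains is differential change over the nine months and unmeasured factors.

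Four other strong readings are not supported either.

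- Different outcome assessors by area: no section says so. Trained nurses and a laboratory technologist collect data without any stated split by area, and all samples go to one laboratory.
- The modified intention-to-treat phrase, "based on group randomized to and using all available data", as a claim that employees were independently randomised: it says only that people are analysed in their allocated group.
- The 16% or 41% as the trial's actual error rate: these rest on an assumed ICC for unadjusted pressure. An ICC of 0.05 implies an area SD of 15.66 × √0.05 = 3.5 mmHg within one occupation in one city, for which the documents give no evidence.
- An allocation with no randomness at all: the coin toss is random. It randomises two areas, not employees.

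Contamination is a legitimate reason to allocate groups. It does not require only one group per arm. The article also leaves the random effects unstated, and a fuller plan may specify them, but no specification creates replication of areas.

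**Conclusion.** The point holds. The allocation as described yields one randomised unit per arm. This contradicts the abstract's account of randomised participants and the individual-level basis of the sample size, and no other section repairs it. Area-specific change over nine months is completely aliased with the intervention, and no mixed model can give a standard error or p-value that includes it. That conclusion follows from the Randomization section alone.

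The numerical consequence is conditional. The nominal 5% error would be about 6%, 16% or 41% at assumed ICCs of 0.001, 0.01 and 0.05 with 94 per arm and no baseline adjustment, and lower to the extent that adjustment removes area variance. The trial cannot show where in that range it lies. The documents do not show that the two areas actually differ; the defect is that the design cannot rule it out.

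**What to change.** **Restate the design.** This comes first, because recruitment began in November 2023 according to the status and timeline section and the areas may already be assigned.

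- Abstract and Study design: describe a two-area controlled before-after comparison with one area per arm, areas allocated by coin toss, employees not randomised.
- Sample size: state that the 80% power assumes no between-area variation in change. State the same assumption for the confidence intervals and p-values.
- Discussion: list one area per arm as a main limitation, and temper the causal and scale-up claims.

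This changes wording only; the price is a more modest claim.

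**Only if allocation has not yet been carried out:** randomise bank branches. The Study setting section reports "There are 210 bank branches with 2,310 workers in the city", about 2,310/210 = 11 workers per branch. Stratify by side of the river and by government or private ownership, so that both arms run on both sides, and fit a random intercept for branch.

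The sample size, or the stated power, must then include a branch design effect. At an assumed branch ICC of 0.05, 2, 5 or 11 participants per branch give design effects of 1.05, 1.20 and 1.50, that is 99, 113 or 141 per arm before attrition (94 times each, rounded up). The other cost is some risk of contamination between branches, whose size the documents do not allow one to judge.

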### Intervention: Education about healthy lifestyle

The intervention will comprise education about healthy lifestyle that includes the concept of metabolic syndrome, risk factors and its prevention, the importance of lifestyle modification such as healthy diet, physical exercise, avoidance of harmful alcohol consumption, smoking cessation and stress management, as well as motivation for changing behavior. The education intervention will be delivered by experts on health education and promotion after the education package is assessed and validated by a nutritionist, physical therapist and psychologist. The education will be delivered in a one-on-one basis at their office or at any other suitable places. Every two weeks, the researcher will send a text message to the participants as a reminder asking whether they have followed the suggested healthy diet, physical activity, and mechanisms of stress management, avoidance of harmful alcohol consumption and smoking. It will also enquire as to whether they recorded their actions using the provided self-report template **(S2 File).** Throughout the intervention, the participants will be encouraged to respond to the messages, ask questions, and seek guidance. Reading materials (Handout) will also be given to each participant with the key messages of “avoid the three whites including: fat, sugar and salt, have a healthy diet, aerobic exercise, avoid sources of trans fats, avoid smoking, avoid unsafe intake of alcohol (≥ 2 drinks per day), manage your stress and avoid sitting for long time”. Additionally, a review meeting with participants will be held at the 3^rd^ and 6^th^ month of the intervention to review the key points of the intervention and reinforce, enhancing health literacy, skills, and motivation among the participants, foster encouragement and support to enhance participants’ commitment and adherence to the intervention, and reassess and identify any obstacles encountered during the intervention, and collaboratively develop strategies to overcome these barriers to change. The primary investigator will supervise the education process. Adherence to the intervention will be improved and monitored by self-report checklists, attendance at review meetings, and text message answers.

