#### At 6^th^ month

Feasibility and acceptability of the intervention will be measured from interventional group only.

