### Data collection and safety monitoring

The trial data safety and adverse effect monitoring committee (DSMC) will be established to monitor the adverse effects of the intervention on participants. Experts in health promotion, laboratory technologists, nurses, and officials will make up the committee. Because the intervention won’t directly involve any invasive procedures or administer drugs that could affect study participants, there won’t be any potential for adverse risks or harms. The DSMC will be used as the protocol for data reporting that minimize bias. The principal investigator will keep track of all adverse events and connect them to the appropriate local health organization if any.

Data will be collected by trained BSc nurses and Laboratory technologist. Waist circumference, blood pressure, and blood sample will be taken at the workplace or another location the participant chooses. Data on knowledge, attitude, and practice about a healthy lifestyle and cardiovascular risk factors will be collected at their office. As well data on the feasibility and acceptability of the intervention will be collected at their office during the review meeting that will be held at the 6^th^ month of the intervention.

The data will only be accessible to the research team, and identifiable information will be kept apart from the rest of the data. Unless the participants have chosen differently, results will only be reported in collective and will not identify them specifically. Data will be securely stored on password-protected computers in the National Centre for Epidemiology and Population Health at the Australian National University. Hard copies of records will be kept in a locked filing cabinet in my office. All research data will be kept for at least five years after publications resulting from the study and securely stored. Following the storage term, all personally identifying information will be eliminated from the data, which will then be archived at the Australian Data Archive (www.ada.edu.au) for use in future research, may be by other researchers as well.

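### Blinding is claimed for all four roles, but it is impossible for the two providers, not credible for participants and not secured for the data collectors

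*Protocol article*

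**What the plan says.** The blinding statement is one sentence in the protocol article, section Randomization. It begins with "The data collectors, the nurse who will offer general advice to the control group" and ends with "the education provider for intervention group, and the participants will all be blinded to the group assignment". It carries no qualification.

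The same section allocates by area. One coin toss decides which side of the river is the control area, and "bank employees who work in the control area will make up the control group"; employees on the other side form the intervention group.

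The section on the intervention describes open delivery. "The education will be delivered in a one-on-one basis at their office or at any other suitable places", and "Every two weeks, the researcher will send a text message to the participants as a reminder". Intervention participants also get a handout, a self-report template and review meetings at months 3 and 6. Under Control group: General health advice, controls get individual advice from a nurse, and the education package and handout follow only when the study ends.

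On measurement, Data collection and safety monitoring says "Waist circumference, blood pressure, and blood sample will be taken at the workplace or another location the participant chooses". The month-6 section says "Feasibility and acceptability of the intervention will be measured from interventional group only".

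**The concern.** An unblinded education trial is normal and is no defect in itself. The problem is that the protocol claims a property its own design does not have.

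The claim matters because several outcomes depend on the person answering or measuring. Attitudes, diet, alcohol, smoking, exercise and stress are reported by participants. Those in the intervention arm are asked every two weeks whether they have followed the same advice on which their practice is later scored. Waist is read from a tape and blood pressure is taken by staff, and the Sample size section names blood pressure as the primary outcome and sizes the trial on systolic pressure. A reader who accepts the Randomization sentence would treat these outcomes as protected from reporting and observer bias, and would rate the risk of bias too low. Any such bias would be expected to favour the intervention.

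**Working it through.** The protocol gives no figure to reproduce on this point. The check sets the blinding sentence beside the other sections, role by role and then outcome by outcome.

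1. **Education provider and control nurse.** The blinding sentence itself identifies each by the arm served. The intervention section gives the education to health-promotion experts, and the control section gives the advice to a nurse. The protocol also has those who deliver the intervention rate its acceptability (Secondary outcomes) and report on fidelity (Process evaluation). Nobody can do that without knowing what they deliver. Blinding is impossible for both.

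2. **Participants.** They are informed of the study objectives before consent (Participants and recruitment). One arm then has one-on-one sessions, two-weekly texts, a self-report template and two review meetings, and rates the intervention at month 6. The other has nurse advice and receives the package later. At most, participants might not know what the other arm receives or what the hypothesis is. The sentence claims more than that, and the claim is not credible.

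3. **Data collectors.** Three features expose them:
   - Work area determines the arm, so a collector who knows the result of the toss knows the arm of everyone in that area.
   - Blood pressure, waist and blood samples may be taken at the workplace. The alternative location is the participant's choice and is not a masking step.
   - Month-6 data are collected from the intervention arm only, at its review meeting. Outcome measures names one set of data collectors (nurses and a laboratory technologist) for all three waves. Nothing separates those who work at month 6 from those who measure at month 9.

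   Blinding is possible here, but not secured.

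4. **Exposure by outcome.**
   - Knowledge, attitudes, practice and stress: most exposed, because unblinded participants supply the answers.
   - Blood pressure and waist: exposed to a lesser degree, and only so far as the assessor knows the arm.
   - Fasting glucose, HDL and triglycerides: much less exposed, because they are measured in a hospital laboratory.

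**The case against.** The best defence concerns the data collectors. Working in a given area reveals the arm only to someone who knows which area was chosen, and the principal investigator tosses the coin. Collectors who are never told the result could measure at workplaces and stay blinded. A reader might infer that the area design makes assessor blinding impossible. The documents do not support that, and the remedy below depends on its being achievable. What remains is that the plan does not secure it, chiefly because of the month-6 contact with one arm.

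A reader might also infer that the laboratory was left out. It was not: Outcome measures counts the laboratory technologist among the data collectors, so the blinding sentence covers that role. No sample-coding step is described, but a condensed article may leave that to the full protocol.

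Nor do the documents say that the advising nurse also collects outcome data. Randomization lists the two roles separately, so overlap should not be assumed.

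Finally, no passage says how blinding will be reported. That the results would carry the claim forward is an inference from the Randomization sentence, though a reasonable one.

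None of this rescues the statement for the educator, the nurse or the participants.

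**Conclusion.** The blinding sentence is wrong for the educator and the control nurse, untenable for participants, and unsupported for the data collectors as the plan is written. It should be corrected. The consequence is confined mainly to the self-reported outcomes and, less strongly, to blood pressure and waist. It should not be extended to the laboratory markers.

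The size of any bias cannot be derived from the documents. A reader might be tempted to assume a bias of a millimetre or two in systolic pressure and convert it into an inflated false-positive rate, using the planned standard deviations and 94 per arm. The protocol gives no source for such a bias. The conversion would also treat participants as independent and start from a nominal 5% error rate, although a single toss allocates two whole areas. Such a figure would be falsely precise, and the point does not need it.

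The conclusion rests on reading the sentence as it stands and on no masking procedure being described in the article. If the full protocol already separates and masks the 9-month assessors, the part about data collectors falls away and the rest stands.

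**What to change.** Replace the blinding sentence in Randomization with one that says:

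- Participants, education providers and the control-group nurse are not blinded.
- Blood pressure and waist at 9 months are measured by data collectors who deliver neither education nor advice, do not collect the month-6 intervention-only data, and are not told which area is the intervention area.
- Laboratory samples are coded without arm or area.

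In the conclusions, describe the knowledge, attitude, practice and stress results as unblinded self-report.

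The cost is a more modest blinding claim and some scheduling of roles among the data collectors. Treatment, visits and sample size do not change. The documents give no staff numbers, so the sponsor must confirm that the existing nurses are enough to keep the roles apart.

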The following methods will be applied to contact and recruit participants: The district headquarters of each bank will get an official letter from the health department of the city administration, after which letters will be issued to each bank branch from the head office of the bank and communications will be made between the managers of each branch and the bank employees. Then, participants will be approached and recruited after being informed about the objectives of the study, inclusion and exclusion criteria, the potential benefits and risks of participation, and ethical considerations of the study. Finally, prior to the start of data collection, written informed consent will be obtained from each participant. Then, the participant will be recruited and screened based on their level of obesity and blood pressure, and those who meet at least one of the two criteria (obesity or high blood pressure) will be included in the trial and will have test for biomarkers (Fasting blood glucose level, Total cholesterol, High density lipoprotein cholesterol, low density lipoprotein cholesterol, and Triglyceride).

To make recruiting effective and to increase participant willingness, the objectives of the study, inclusion and exclusion criteria, ethical considerations of the study, the advantages of the study and their rights even to stop in the middle of the procedure will be explained to participants. The participants will be informed that their participation in this study is very important for the success of the study and for paving the way for the development of the policy in this area. Additionally, they will be told that there is no risk except some discomforts to them in taking part in this study, and that all data obtained from them would be kept confidential via a password with no requirement that their identities be recorded, and results will also be communicated to them at the end of the study. They will also be told that even if they do not meet the requirements to participate in the study, they will still get advice on living a healthy lifestyle and about seeking medical counsel if they exhibit any signs of metabolic syndrome.

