#### Exclusion criteria

Bank workers who have at least one of the NCEP: ATP III metabolic syndrome criteria but with dietary restrictions and absolute contraindication for physical activity due to musculoskeletal, neurological, vascular, lung and cardiac problems, pregnant mothers, those who have a plan to be pregnant within the intervention months and diagnosis of severe psychiatric disorders, significant cognitive impairment, and those who will not available throughout the program will be excluded from the study.

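### Individuals are screened and enrolled after their area's arm is fixed and known to the investigator, so who enters each arm can depend on the arm

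*Protocol article*

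**What the plan says.** The Randomization section of the protocol article gives the steps in this order. Of the two parts of the city, "one will be randomly selected as the control area using a coin tossing randomization procedure by a principal investigator". Workplace then decides the arm: "bank employees who work in the control area will make up the control group", and likewise for the intervention area. The last step is: "Finally, each individual participant will be screened based on the inclusion and exclusion criteria, up until the target sample size is reached".

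The same section says that the data collectors, the nurse advising the control group, "the education provider for intervention group, and the participants will all be blinded to the group assignment". The investigator who tosses the coin is not on that list, and neither is anyone described as a recruiter. The intervention section adds: "The primary investigator will supervise the education process".

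Under Participants and recruitment, letters go from the city health department to the banks and on to the branches, and "communications will be made between the managers of each branch and the bank employees". After that, "participants will be approached and recruited after being informed about the objectives of the study", and consent is taken. Under Exclusion criteria, "those who will not available throughout the program will be excluded from the study".

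No section places listing, consent or baseline measurement before the toss.

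**The concern.** When groups are allocated first and individuals enrolled afterwards, randomization no longer protects the make-up of the arms. Anyone who knows the toss knows a candidate's arm from the candidate's workplace, before that candidate is approached.

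Three steps then leave room for the arm to influence who enters:

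- the choice of whom to approach;
- the candidate's willingness to consent;
- the judgement that someone will be available for the whole programme.

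The third is open to this because the programmes differ. One area receives one-on-one education, fortnightly text messages and review meetings at months 3 and 6. The other receives individual general advice.

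At stake is the comparability of the arms in motivation and readiness to change. A larger sample does not cure a difference of that kind.

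**Working it through.** **1. Order and knowledge of allocation.** These follow from setting the sections side by side.

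- Toss by a principal investigator, then arm by workplace, then individual screening until the target is filled (Randomization).
- The investigator knows the toss and supervises the education (intervention section), so is aware of the allocation throughout enrolment.
- Blinding is stated for data collectors, control nurse, educator and participants. Nothing is stated for the person who approaches employees.
- Pool: 2,310 workers in 210 branches (Study setting) for 226 places (Sample size), so 2,310 / 226 = 10.2 workers per place before eligibility is applied. The article does not give the number eligible, nor the order in which staff are approached.

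**2. The plan's own sample size.** Inputs from the Sample size section: SDs 15.0 and 16.3 mmHg, means 107.8 and 114.2, z-values 1.96 and 0.84.

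n per arm = (15.0² + 16.3²)(1.96 + 0.84)² / 6.4² = 490.69 × 7.84 / 40.96 = 93.92, rounded up to 94. The stated figure reproduces.

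**3. Illustration of size.** The article gives no figure for a selection shift, so the shift b below is an assumption. The setting is no true effect, an unadjusted comparison and 94 analysed per arm.

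SE = √(490.69 / 94) = 2.285 mmHg

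Two-sided rejection rate = 1 − Φ(1.96 − b/SE) + Φ(−1.96 − b/SE)

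| Assumed shift b (mmHg) | b / 6.4 | Rejection rate |
|---|---|---|
| 0 | 0% | 5.0% |
| 1 | 16% | 7.2% |
| 2 | 31% | 14.1% |
| 3 | 47% | 25.9% |
| 4 | 63% | 41.7% |

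**4. What the planned analysis removes.** The Statistical analysis section compares changes from baseline to nine months, and the abstract says baseline variations are accounted for. For a comparison of changes, the bias is the shift at nine months minus the shift at baseline. A difference in level that stays constant cancels. Selection that alters the nine-month course does not. The table therefore has to be read as the shift left after adjustment. The article gives no baseline-to-follow-up correlation, so I do not carry the adjusted calculation further.

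**5. Timetable.** Recruitment runs from 20 November to 29 December 2023, which is 39 days or about 5.6 weeks. Nine months from 29 December 2023 is 29 September 2024, and the project closes in September 2024.

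**The case against.** The strongest reply is the blinding sentence. If data collectors and participants really do not know the arm, willingness cannot respond to it, and the recruitment text does not say that candidates are told their arm. This would reduce the risk if it held. It is hard to sustain, because the educator gives only education and the nurse only general advice, each in one area. It also covers neither the investigator nor an unnamed recruiter.

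Second, the order rests largely on the word that opens the last step. The recruitment section uses that word loosely, and the abstract speaks of participants being randomized. Allocation first remains the natural reading, and nothing in the article states the reverse.

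Third, the analysis adjusts. Besides the demographic covariates, the Statistical analysis section lists level of knowledge, attitudes and practice, which is measured at baseline in both groups and is a partial proxy for readiness to change. The waist, blood pressure and laboratory criteria are objective. Both points stand and narrow the concern. Neither reaches unmeasured willingness or judged availability.

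A reader might go further and infer that employees are a convenience sample, that the investigator personally picks them, or that nobody at enrolment is unaware of the arm. The article says none of this. It is silent on the order of approach, which a condensed article may leave to the full protocol.

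**Conclusion.** The point holds as a risk of recruitment bias. On the natural reading, areas are allocated before individuals are screened, the investigator knows the result, and the stated blinding does not cover whoever approaches employees. Entry to each arm can therefore depend on the arm.

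A reader might infer that the arms will in fact be unbalanced, or that 14% or 26% is this trial's false-positive rate. The article supports neither. No selection shift is given or can be derived from it. The rates come from assumed shifts of 2 and 3 mmHg in an unadjusted comparison. Their 5% starting point treats 188 people as individually allocated, whereas two areas are allocated. The figures show only that a residual shift of about a third to a half of the planned 6.4 mmHg would matter.

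Confidence is moderate on the size of the problem and higher on the order of steps.

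**What to change.** **If the toss has not been made:** complete screening (including the availability exclusion), consent and baseline measurement in both areas, and only then toss the coin.

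**If it has been made**, which is likely because recruitment opened on 20 November 2023:

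- have employees approached from complete branch staff lists, in a fixed or random order, by recruiters who do not know the allocation;
- apply the availability exclusion by one written rule in both areas;
- report the numbers approached, eligible and consented by arm in the CONSORT diagram that is already planned. The trial flow figure was not visible to me and may already show some of these counts.

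**Cost.** Under the first option, education starts only when recruitment ends, a wait of about six weeks for the earliest recruits. Nine months from the anticipated end of recruitment falls on 29 September 2024, so this uses up the slack before the September 2024 close. The second option costs mainly the staff lists and a recruiter kept apart from the education.

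Neither option removes the confounding of arm with area that comes from having one area per arm. That is a separate problem.
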